### Safety

Safety will be assessed by measuring the frequency of serious adverse events (SAE). A serious adverse event (SAE) in the trial is defined as:
any event that is fatal or immediately life threatening, permanently disabling, severely incapacitating or requires prolonged hospitalization **OR**any event that may jeopardize the patient and requires medical or surgical intervention to prevent one of the outcomes listed above **AND**which the attending physician perceives may be directly related to enrollment in the clinical trial.

Investigators will report severe adverse events to the clinical coordinator. An independent Data and Safety Monitoring Board (DSMB) will receive a detailed written report and evaluate whether the SAE is attributable to ECCO_2_R. SAE will be considered to be study-related if the event follows a reasonable sequence from a study procedure and could be produced by the study procedure. SAE will be considered not study related if they are thought to be primarily related to the underlying disease and its sequelae.

Other adverse events not fulfilling the above definition are recorded as ECCO_2_R related adverse events (ECCO_2_R-AE) and classified as:

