**mechanical**
difficulties upon catheter insertion (i.e. need for >2 attempts at catheter insertion during primary placement procedure);pump malfunction (i.e. need for >2 consecutive interventions during the same treatment with the same blood circuit, regardless of the need for stopping the procedure or for replacement of the pump);membrane lung clotting (leading to interruption of ECCO_2_R and/or circuit replacement);catheter displacement;cannula thrombosis;air in the circuit;tubing rupture;system leaks;**clinical**:
hemolysis (i.e. serum free hemoglobin ≥ 100 mg/L or hematocrit reduction not related to hemorrhage or other causes of blood loss, jaundice, hemoglobinuria, impaired renal function);bleeding (related to cannula insertion, and/or at cannula site; bleeding is considered “significant” if requires administration of ≥1 unit of packed red cells);hemodynamic instability (see criteria in the ‘Treatment of participants’ paragraph);ischemic/gangrenous bowel;pneumothorax;renal complications (i.e., occurrence of serum creatinine >1.5 mg/dl after initiation of ECCO_2_R);infectious complications (i.e., occurrence of culture-proven new infection after initiation of ECCO_2_R);thromboembolic complications (i.e., occurrence of deep venous thrombosis or pulmonary embolism after initiation of ECCO_2_R);thrombocytopenia (platelet count below 50,000/mm^3^);hypofibrinogenemia (i.e. fibrinogen < 1.5 g/L);neurologic complications (i.e. occurrence of cerebral infarction, or clinical seizure, or cerebral hemorrhage or cerebral edema after initiation of ECCO_2_R).

Each SAE will be notified by the investigator to the coordinating center, DSMB and ethics committee within 24 hours of occurrence. A detailed report will be sent by the investigator within 5 days of occurrence. The DSMB will examine every report immediately and will take every measure needed to ensure patients safety. Moreover, the DSMB will also meet every 30 enrolled patients to perform all necessary safety analyses. The DSMB can irrevocably halt the trial if the data analysis would show risks for patients’ safety.

An appropriate insurance policy, covering all enrolled patients for possible harm will be activated before enrollment of the first patient.

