#### Evaluation of secondary endpoints

All components of the primary composite endpoint (singleton) will be examinated separately as independent proportion. The cumulative incidence of sepsis, hypercapnic respiratory failure, hypoxemic respiratory failure, prolonged mechanical ventilation >28days, tracheostomy and endotracheal intubation will be estimated with the Gooley method, to take into account the competitive risk of death, and compared with the Grey test. The Fine and Grey model will be used to estimate adjusted HR and their 95% CI. In addition, overall survival (OS) will be analyzed with Kaplan-Meier method and compared with the log rank test. A Cox proportional hazard model (if appropriate) will be used to estimate the Hazard Ratios (HR) and the 95% CI.Hospital length of stay and ICU length of stay will be described in each arm as median and interquartile range; they will be compared with the Wilcoxon rank sum test. The 95% confidence interval (CI) of the mean difference of measure will be estimated with a bootstrap method.Hospital mortality will be expressed as rate and a Chi square test will be used to evaluate the difference between the two groups.Incidence of adverse events and severe adverse events will be expressed as rate and a Chi square test will be used to evaluate the difference between the two groups.

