## Discussion

The consistency of the data from systematic reviews and matched cohort studies [12–14], and the observation of the continuous increase use of ECCO_2_R despite the lack of solid evidence [12] confirm that the equipoise regarding the use of ECCO_2_R justifies our randomized clinical trial to evaluate whether patients with respiratory acidosis refractory to NIV should be intubated and take the risks associated with invasive mechanical ventilation, or should be connected to ECCO_2_R to avoid intubation, but run the risk of the potentially serious ECCO_2_R-related complications. Moreover, this trial may allow clinicians and hospital managers to know whether this treatment should be made available or should be avoided since inappropriate and associated to serious side effects.

One possible limitation of our study design is that it doesn’t include long-term patient-centered outcome measures; however, we feel that long-term outcome measures would add complexity to our pragmatic trial design and should be investigated in future trials, especially after clear evidence on shorter-term efficacy and safety are gathered.

The ORION trial, owing to its pragmatic nature, planned sample size and composite primary outcome is expected to provide valuable and definite answers to these important research questions. Hypercapnic exacerbation of COPD represent a significant clinical (prognosis), social (quality of life) and economic (health-care costs) burden worldwide and the avoidance of invasive mechanical ventilation through the application of ECCO_2_R (combined with NIV) may significantly impact the natural history of COPD itself.

Presently, the interest of the scientific community for the subject is very high, and this work is thus potentially highly significant in the field of respiratory intensive care medicine.

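### Four non-device-specific types of non-serious adverse event can be counted only in Group B, yet the adverse event rate is tested between arms

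*Protocol article*

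**What the plan says.** The Safety section defines serious adverse events first, without reference to ECCO2R exposure. It then deals with everything else: "Other adverse events not fulfilling the above definition are recorded as ECCO_2_R related adverse events (ECCO_2_R-AE) and classified as". A mechanical list of 8 items and a clinical list of 11 follow. No other category for non-serious events is given for either arm.

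Four clinical items start their clock at the device:
- on clotting, the list has "thromboembolic complications (i.e., occurrence of deep venous thrombosis or pulmonary embolism after initiation of ECCO_2_R";
- on infection, it has "infectious complications (i.e., occurrence of culture-proven new infection after initiation of ECCO_2_R";
- on kidney function, it has "renal complications (i.e., occurrence of serum creatinine >1.5 mg/dl after initiation of ECCO_2_R";
- on the brain, it has "neurologic complications (i.e. occurrence of cerebral infarction, or clinical seizure, or cerebral hemorrhage or cerebral edema after initiation of ECCO_2_R".

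Bleeding is tied to the cannula: "bleeding (related to cannula insertion, and/or at cannula site". The mechanical items concern the circuit or its catheter. The other six clinical items (hemolysis, hemodynamic instability, bowel ischemia, pneumothorax, thrombocytopenia, hypofibrinogenemia) have no such clause.

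Secondary outcomes lists the incidence of adverse events and refers to the Safety section for the definition. Evaluation of secondary endpoints adds: "Incidence of adverse events and severe adverse events will be expressed as rate and a Chi square test will be used to evaluate the difference". The comparison is Group A against Group B.

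**The concern.** New infection, raised creatinine, venous thromboembolism and seizure or stroke are not specific to an extracorporeal circuit. They can occur in a ventilated COPD patient in either arm, for example after intubation. Group A receives no ECCO2R, so a Group A patient cannot satisfy a definition that begins at its initiation.

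The two arms are therefore measured with different rulers and then tested as if with one. The observed difference mixes device harm with background morbidity, and the p value does not test equal risk. The Discussion presents the trial as a choice between two sets of risks: whether patients "should be intubated and take the risks associated with invasive mechanical ventilation" or accept the complications of ECCO2R. For non-serious events of these four types, only the ECCO2R side is counted.

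**Working it through.** The plan states no figure for this outcome, so there is nothing to reproduce. The check sets the definitions against the test and then sizes the effect.

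**Inputs from the protocol.** 142 patients per arm and no crossover (Sample size); no ECCO2R in Group A (Treatment of participants); item definitions (Safety); chi-square comparison (Evaluation of secondary endpoints).

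**Assumptions.** Two-sided 5% level for this test; background risk r of the four event types, equal in both arms; rate o of other countable events, equal in both arms and independent of the four types. The documents give none of these.

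**Step 1: size of the distortion.** Let A and B be the true proportions with any adverse event, and q the share of Group A whose only adverse events are non-serious events of the four types.
- True difference = B − A.
- Difference as written = B − (A − q).
- Overstatement = q, that is 5, 10 or 20 percentage points at q = 5%, 10% or 20%.

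**Step 2: with substantial device harm.** Suppose device-caused events occur in 50% of Group B. Trial hypothesis and main objective reports complications in almost half of the ECCO2R patients in an earlier cohort; carrying that over is an assumption. With no other countable events, B = 1 − (1 − 0.5)(1 − q).

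| q | B | True difference (B − q) | Difference as written |
|---|---|---|---|
| 5% | 52.5% | 47.5 points | 52.5 points |
| 10% | 55% | 45 points | 55 points |
| 20% | 60% | 40 points | 60 points |

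The test is significant on either count; only the size of the excess is wrong.

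**Step 3: no device harm, Group A counts zero (extreme case).** For k of 142 against 0 of 142, the uncorrected chi-square is 3.03 (p = 0.082) at k = 3 and 4.06 (p = 0.044) at k = 4. With continuity correction, k = 5 gives p = 0.071 and k = 6 gives p = 0.039. The false-positive rate is P(X ≥ 4), or P(X ≥ 6) with correction, for X ~ Bin(142, r):
- r = 3%: 62% (25% corrected)
- r = 5%: 93% (72%)
- r = 10%: over 99% (over 99%)

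**Step 4: no device harm, other events also counted.** Group A's countable rate is o and Group B's is 1 − (1 − o)(1 − r). For example, o = 5% and r = 5% give 5% against 9.75%. Exact rejection probabilities, uncorrected, 142 per arm:

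| Other countable events, each arm (o) | r = 3% | r = 5% | r = 10% |
|---|---|---|---|
| 0% (extreme case) | 62% | 93% | >99% |
| 5% | 16% | 32% | 79% |
| 10% | 11% | 21% | 59% |
| 20% | 8% | 13% | 35% |

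**Step 5: both arms counted alike.** The same test then rejects about 5% of the time (4.4%, 4.8% and 4.9% at event rates of 3%, 5% and 10%).

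**The case against.** **The high false-positive rates are a corner case.** They need Group A to count exactly zero events and the device to cause none. Six clinical items carry no initiation clause, and hemodynamic instability is itself an intubation criterion in Group A. If those items count there, the rates fall to those in the lower rows of the Step 4 table. If device harm is near that of the earlier cohort, the test's conclusion does not change at all. This stands, and a reader should not infer that a spurious finding of harm is near certain.

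**The wording admits two readings.** If the ECCO2R-AE heading governs, all 19 items are Group B device complications. The six other items then also have no stated route into Group A, and the chi-square test has little meaning. If the heading is only a label, the fault is confined to the items whose own wording requires the device. The wording does not settle which reading was meant, but on either one the four item types are one-sided and the comparison needs changing.

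**A count of thirteen items that only ECCO2R patients can meet is tempting.** It would be the 8 mechanical items, bleeding and the four above. It is too firm: the items on repeated catheter insertion attempts and on catheter displacement do not name ECCO2R.

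**Control-arm harm is measured elsewhere.** Septic shock, prolonged ventilation and death are in the primary endpoint. Sepsis, intubation and tracheostomy are compared between arms, and the SAE definition does not depend on exposure. It would therefore be wrong to infer that harms of the invasive pathway go unmeasured. None of these outcomes captures non-serious renal, infectious, thromboembolic or neurologic events in Group A.

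**The full protocol may settle it.** A follow-up window may well be given there. The point does not rest on a missing window: the definitions, the outcome and the test are all stated in the article, and they do not fit together.

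**Conclusion.** The point holds for non-serious adverse events. The stated definitions count four non-device-specific event types in Group B whatever their cause and never in Group A, and the plan tests the resulting rate between arms. The difference is overstated by q, against ECCO2R. That follows from the definitions given that Group A receives no ECCO2R; the value of q does not, and 5 to 20 points is only what q of 5% to 20% would give.

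The inflation of the false-positive rate is real but its size is uncertain: from 8% (r = 3%, o = 20%) to over 99% (r = 10%, Group A at zero) across the assumed values, all without device harm. The documents do not support taking the upper end as the expected result.

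The SAE rate, the DSMB's review and the primary endpoint are not affected by this point. It concerns one secondary safety outcome and should be corrected before data collection starts.

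**What to change.** - **Safety, clinical list:** in the renal, infectious, thromboembolic and neurologic items, start the count at randomization instead of at ECCO2R initiation. Define bleeding as any bleeding, with cannula-related bleeding as a subset.
- **Safety, introductory sentence:** record clinical adverse events in both arms over the same window, with relatedness to ECCO2R as a separate item. A window from randomization to day 28 would match the primary endpoint; that choice is a proposal.
- **Evaluation of secondary endpoints:** compare clinical adverse events between arms, and describe mechanical events in Group B only, without a test.

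The cost is rewording in these places and entry of the clinical items for Group A in the eCRF. Trial status says that recruitment had not begun at the time of writing, so the eCRF could still be changed at that point; control events left uncollected may not be recoverable later. The downside is more data entry for control patients and a higher reported adverse event rate in Group A.

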**mechanical**
difficulties upon catheter insertion (i.e. need for >2 attempts at catheter insertion during primary placement procedure);pump malfunction (i.e. need for >2 consecutive interventions during the same treatment with the same blood circuit, regardless of the need for stopping the procedure or for replacement of the pump);membrane lung clotting (leading to interruption of ECCO_2_R and/or circuit replacement);catheter displacement;cannula thrombosis;air in the circuit;tubing rupture;system leaks;**clinical**:
hemolysis (i.e. serum free hemoglobin ≥ 100 mg/L or hematocrit reduction not related to hemorrhage or other causes of blood loss, jaundice, hemoglobinuria, impaired renal function);bleeding (related to cannula insertion, and/or at cannula site; bleeding is considered “significant” if requires administration of ≥1 unit of packed red cells);hemodynamic instability (see criteria in the ‘Treatment of participants’ paragraph);ischemic/gangrenous bowel;pneumothorax;renal complications (i.e., occurrence of serum creatinine >1.5 mg/dl after initiation of ECCO_2_R);infectious complications (i.e., occurrence of culture-proven new infection after initiation of ECCO_2_R);thromboembolic complications (i.e., occurrence of deep venous thrombosis or pulmonary embolism after initiation of ECCO_2_R);thrombocytopenia (platelet count below 50,000/mm^3^);hypofibrinogenemia (i.e. fibrinogen < 1.5 g/L);neurologic complications (i.e. occurrence of cerebral infarction, or clinical seizure, or cerebral hemorrhage or cerebral edema after initiation of ECCO_2_R).

Each SAE will be notified by the investigator to the coordinating center, DSMB and ethics committee within 24 hours of occurrence. A detailed report will be sent by the investigator within 5 days of occurrence. The DSMB will examine every report immediately and will take every measure needed to ensure patients safety. Moreover, the DSMB will also meet every 30 enrolled patients to perform all necessary safety analyses. The DSMB can irrevocably halt the trial if the data analysis would show risks for patients’ safety.

An appropriate insurance policy, covering all enrolled patients for possible harm will be activated before enrollment of the first patient.

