#### Group B: Standard of care plus ECCO_2_R

NIV is applied and managed with the same modalities and at the same conditions as in Group A (standard of care).

After setting NIV, percutaneous vascular access is provided using a double lumen catheter inserted in the internal jugular vein or in the femoral vein (14F, Joline GmbH & Co. KG, Germany). An ECCO_2_R device will be used (DECAPsmart, Medica S.p.A.- Intensivecare s.r.l., Salerno, Italy). Blood flow is driven by a roller nonocclusive pump (0–450 mL/min) through a polymethylpentene artificial lung (priming volume, 200 mL; contact surface area, 0.8 m^2^; maximum blood flow rate, 450 mL/min) that is connected to a fresh gas flow source delivering 100% oxygen at a constant rate of 8 L/min. A starting dose of heparin (80 IU/kg bolus followed by ∼18 IU/kg/ hour infusion) will be delivered by using a syringe pump included in the system. Continuous infusion of heparin is hence titrated to maintain values of activated partial thromboplastin time (aPTT) in the range 35-80 sec or aPTT ratio of 1.5-2.0; aPTT is checked approximately every 2-3 hours during the first 6 hours from therapy initiation; afterwards, aPTT is checked every 6 hours. ECCO_2_R will be continued for at least 24 hours.

Intubation criteria are the same as in Group A (standard of care).

Weaning from ECCO_2_R must always precede weaning from mechanical ventilation. ECCO_2_R will be interrupted while keeping mechanical ventilation (invasive or non-invasive) when all of the following are achieved for at least 12 hours:
respiratory rate<25 breaths/min;pH>7.35;arterial PCO_2_<20% of the baseline value;absence of use of the accessory muscles or paradoxical abdominal movements.

Criteria to (a) *run formal assessment of discontinuation* from mechanical ventilation (invasive or non-invasive) through a daily spontaneous breathing trial (SBT); (b) to be defined as “weaned from mechanical ventilation” (invasive or non-invasive) are the same as in Group A (standard of care).

Use of ECCO_2_R is stopped and device (and catheter) removed in the following situations:
Air embolus in the extracorporeal circuitCircuit clotting leading to an abrupt stop of extracorporeal blood flowDevice malfunction leading to abrupt stop of extracorporeal blood flowSevere thrombocytopenia (< 29,000/mm^3^)Fibrinogen < 1g/L or fibrinogen < 1.5 g/L with diffuse bleedingAnytime the physician in charge believes that the protocol may be compromising patient’s outcome

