Interruptions of ECCO_2_R (for any cause) lasting longer than 6 hours are to be considered ‘treatment failure’ and lead to termination of the experimental protocol.

All concomitant therapies foreseen by the standard of care of enrolled patients are allowed.

Post-trial care will be delivered according to the standard of care for AECOPD patients.

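### The pump-malfunction event needs more than two consecutive interventions, so a single failure that stops blood flow and ends ECCO2R can miss the item and has no other mechanical category

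*Protocol article*

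**What the plan says.** Two parts of the protocol article deal with failure of the device.

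- **Safety, mechanical list of ECCO2R-related adverse events.** The pump item reads "pump malfunction (i.e. need for >2 consecutive interventions during the same treatment with the same blood circuit, regardless of the need for stopping the procedure", and the clause goes on to treat pump replacement in the same way. In the same list, the clotting item reads "membrane lung clotting (leading to interruption of ECCO_2_R and/or circuit replacement", with no minimum count.
- **Group B: Standard of care plus ECCO2R.** The article says that ECCO2R "is stopped and device (and catheter) removed in the following situations". One of those situations is a device malfunction that brings blood flow to a sudden halt. No number of interventions is attached to it.

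Three other provisions bear on whether such a failure is recorded:

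- The SAE definition in Safety includes "any event that may jeopardize the patient and requires medical or surgical intervention to prevent one of the outcomes listed above", if the attending physician perceives a possible direct relation to enrolment.
- The lead-in to the mechanical and clinical lists says "Other adverse events not fulfilling the above definition are recorded as ECCO_2_R related adverse events" and then sorts them by those lists.
- The Group B section says that ECCO2R interruptions from any cause "lasting longer than 6 hours are to be considered" treatment failure, which ends the experimental protocol.

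Adverse events as defined in Safety are one of the secondary outcomes. Under the evaluation of secondary endpoints they are expressed as rates and compared by a chi-square test.

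**The concern.** The pump item counts repeated interventions. It does not count the consequence that matters most for the therapy, namely that it stopped. Read literally, a pump that needs three consecutive interventions and keeps running is an event, while a pump that stops once and is taken out after two or fewer interventions is not. The clotting item in the same list works the other way: one occurrence that interrupts treatment is enough.

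The Discussion frames the trial as weighing avoided intubation against ECCO2R-related complications. Mechanical events arise in patients connected to the device, so any undercount falls on Group B and makes the device look more reliable than it was. If sites resolve the gap differently, the rate also comes to depend on local reading of the definition.

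**Working it through.** The article states no figure to reproduce, and no arithmetic decides the point. The check applies the definition to the stopping situations and then tests each other route by which the event could be recorded.

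**Step 1: what the pump item requires.** The item is introduced by *i.e.*, so it is a definition and not an example. More than two consecutive interventions means at least three. The closing clause makes stopping or pump replacement irrelevant to whether the item is met.

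**Step 2: apply it.**

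| Course | Interventions needed | Pump-malfunction item |
|---|---|---|
| Blood flow stops abruptly, device removed | 0, 1 or 2 | Not met |
| Blood flow stops abruptly, repeated consecutive restart attempts, device removed | 3 or more | Met |
| Blood flow never stops | 3 or more, consecutive | Met |

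The gap is the first row.

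**Step 3: compare the Group B stopping list with the adverse-event lists.**

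- Air embolus in the circuit: matched by the item on air in the circuit.
- Circuit clotting: matched by membrane lung clotting or cannula thrombosis, for clots at those sites.
- Platelets below 29,000/mm³: within the thrombocytopenia item (below 50,000/mm³).
- Fibrinogen below 1 g/L, or below 1.5 g/L with diffuse bleeding: within the hypofibrinogenemia item (below 1.5 g/L).
- Device malfunction with abrupt loss of flow: the natural match is the pump item, which is met only from the third intervention.
- Physician's judgement: no matching event is to be expected.

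Device malfunction is therefore the specific stop reason whose natural counterpart carries an intervention threshold.

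**Step 4: other mechanical items.** These are insertion difficulty, lung clotting, catheter displacement, cannula thrombosis, air, tubing rupture and leaks. Some sudden losses of flow will fall under one of them. None names failure of the pump or console itself.

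**Step 5: other routes of capture.**

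- *SAE.* This route needs a serious outcome, or jeopardy that requires intervention together with perceived relatedness. A patient who returns to NIV alone without immediate danger need not qualify.
- *Other ECCO2R adverse event.* The lead-in says that such events are recorded, but the list that follows has no residual category. The event could be entered without a class, placed under the nearest label, or left out.
- *Treatment failure.* This identifies the patient if the interruption exceeds 6 hours. It is a label for ending the protocol. It is not among the secondary outcomes, and the evaluation of secondary endpoints does not mention it.

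What remains is an isolated pump or console failure that needs two or fewer interventions and is not an SAE.

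**The case against.** The strongest reply is that this is a narrow gap in one label and that the failure does not vanish. This largely stands. A reader might infer that the worst pump failures go uncounted, but the article does not support that. A failure that endangers the patient can be an SAE, other adverse events are said to be recorded, and a long interruption is a treatment failure.

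Three further inferences also go too far:

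- **That the interventions must come before the failure.** The item speaks of a need for consecutive interventions and sets no order, so restart attempts after a stop can count towards the threshold.
- **That the DSMB would be blind to device failures.** The article describes no device-failure tables. The DSMB is notified of each SAE, examines every report, and meets every 30 enrolled patients for the safety analyses it considers necessary. Nothing confines it to the pump label.
- **That a number of missed patients can be given.** An assumed failure rate of 3% to 10% among 142 Group B patients gives 142 × 0.03 = 4.3 to 142 × 0.10 = 14.2. The rate is not in the article, and the sum treats every failure as a pure pump failure with two or fewer interventions and no other mechanical record. It is at most an illustrative ceiling.

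It is also fair to say that a stopping rule and an event classification serve different purposes, so the two sections do not strictly contradict each other. What the reply does not answer is that the article states the pump definition positively and feeds it into a named secondary outcome. The gap is therefore a stated rule, not a detail left to the eCRF or the analysis plan.

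**Conclusion.** The point holds in a limited form. The pump-malfunction item omits a single pump or console failure that stops blood flow and ends treatment after two or fewer interventions, and no other mechanical category names that event. A non-serious failure of this kind can be lost from the mechanical adverse-event rate or classified inconsistently. The direction of the error is to understate device failures in Group B.

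The size is unknown, because the article gives neither a failure rate nor a distribution of interventions per failure. The conclusion rests on reading *i.e.* as a full definition and on the absence of a residual category in the mechanical list. The primary outcome, its analysis and the sample size are untouched. This is a worthwhile correction to one component of a secondary outcome, and it does not threaten the trial's main result.

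**What to change.** Reconcile the pump item in the mechanical list with the device-malfunction entry in the Group B stopping list by widening the event definition. Pump malfunction would be recorded when either of the following holds:

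1. any single malfunction stops extracorporeal blood flow, or leads to removal of the device or replacement of the pump; or
2. more than two consecutive interventions are needed during one treatment on the same circuit, as now.

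Record the two limbs in separate fields and report them separately, so that failures ending therapy are not blended with repeated interventions. The stopping criteria themselves need no change for this purpose.

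The cost is one extra eCRF field and a slightly higher reported mechanical event rate. The Trial status section says that recruitment had not begun at the time of writing, so at that point no collected data would have needed recoding.

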### Sample size

A two-sided log-rank test with an overall sample size of 284 subjects (142 in the control group and 142 in the treatment group) achieves 90% power at a 0.05 significance level to detect a hazard ratio of 0.67 when the proportion surviving without events in the control group is 40% (we estimated a combined proportion of death, prolonged mechanical ventilation, septic shock, severe hypoxemia and second episode of COPD exacerbation of 60% [23–33]). The study will last 25 months of which 24 months to accrual and 1 month of follow up. No subject will drop out of the control/treatment group. We assume no cases of switch (crossing-over) between the arms: the proportion of the control group that switches to a group with a risk rate equal to the treatment group is equal to zero (and vice versa).

This study has been designed to demonstrate a relative increase of 35% in the event free survival (from 40% to 54%), assuming the above-mentioned parameters.

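### The hematocrit part of the hemolysis definition has no minimum fall and does not exclude dilution, and its list can be read three ways, so the non-serious hemolysis rate is non-specific and not comparable across sites

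*Protocol article*

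**What the plan says.** Under Safety, the protocol article lists clinical ECCO2R-related adverse events that do not meet its definition of a serious adverse event. One item is "hemolysis (i.e. serum free hemoglobin ≥ 100 mg/L or hematocrit reduction", and the hematocrit alternative reads in full "hematocrit reduction not related to hemorrhage or other causes of blood loss, jaundice, hemoglobinuria, impaired renal function". The first limb has a numeric limit; the second has none. Neighbouring items do have limits: serum creatinine above 1.5 mg/dl, platelets below 50,000/mm³ and fibrinogen below 1.5 g/L.

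The section on Group B describes a "polymethylpentene artificial lung (priming volume, 200 mL; contact surface area, 0.8 m^2^; maximum blood flow rate, 450 mL/min" and states that "ECCO_2_R will be continued for at least 24 hours". It does not say what the prime contains or whether it is returned to the patient.

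Secondary outcomes includes the incidence of adverse events as the Safety paragraph defines them. Evaluation of secondary endpoints adds: "Incidence of adverse events and severe adverse events will be expressed as rate and a Chi square test will be used" to compare the two groups.

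**The concern.** A hematocrit can fall without any red-cell destruction or blood loss. Connection to a primed circuit dilutes the blood, and so do intravenous fluids. Neither is hemorrhage or blood loss, so the words of the second limb do not remove them. Connection happens only in Group B, so this source of false cases acts in one direction.

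The wording of the list adds a second problem. The text does not say how jaundice, hemoglobinuria and impaired renal function relate to the hematocrit fall, and up to twenty sites may resolve this differently. Hemolysis is a main blood-damage signal for a roller-pump membrane circuit, and the Discussion presents the trial as weighing avoided intubation against device harm. A count that mixes dilution with hemolysis, in proportions that depend on how each site reads the sentence, is of little use for that purpose.

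**Working it through.** The plan states no expected hemolysis rate or hematocrit change, so there is no figure of its own to reproduce. The check has three parts.

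**1. The three readings of the list**

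- *Excluded causes.* Jaundice, hemoglobinuria and renal impairment continue the list of things the fall must not be related to. A fall alone then suffices. A fall related to hemoglobinuria or jaundice, both signs of hemolysis, would be left out, while dilution would count.
- *Separate criteria.* Each term is a further alternative. A fall alone again suffices. Impaired renal function by itself also becomes hemolysis, although renal complications have their own item in the same list.
- *Accompanying signs.* The fall counts only with one or more of the signs. Dilution alone then gives no cases. The text contains no joining word that says so, and does not say how many signs are needed. If one is enough, a trivial fall in a patient with renal impairment still counts.

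**2. Size of the dilution**

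From the documents: prime P = 0.2 L, stated for the artificial lung. Assumed: blood volume V, starting hematocrit H, and a prime that contains no red cells and is fully retained.

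Expected fall = H × P / (V + P).

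| V (L) | H (%) | Calculation | Fall (points) |
|---|---|---|---|
| 4.9 | 40 | 40 × 0.2 / 5.1 | 1.57 (40.0 to 38.4) |
| 5.6 | 36 | 36 × 0.2 / 5.8 | 1.24 |
| 4.2 | 45 | 45 × 0.2 / 4.4 | 2.05 |

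The wider range takes 60 to 70 mL/kg, 50 to 120 kg (only the upper weight limit is in the Exclusion criteria) and hematocrit of 30 to 50%:

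- smallest fall: 30 × 0.2 / (8.4 + 0.2) = 0.70 points
- largest fall: 50 × 0.2 / (3.0 + 0.2) = 3.1 points

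The expected change is a fall in every case.

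**3. How often one pair of readings would show a fall**

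An expected fall is not an observed fall in each patient. Let s be the standard deviation of one reading (assay plus short-term variation), assumed to be 0.5 to 2 points. Then

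P(any observed fall) = Φ(fall / (√2 × s)).

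For a 70 kg patient with V = 4.9 L and H = 40% (fall 1.57):

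| s (points) | P(any fall) |
|---|---|
| 0.5 | 99% |
| 1 | 87% |
| 1.5 | 77% |
| 2 | 71% |

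Over the wider range, the lowest value is Φ(0.70 / 2.83) = 60% and the highest is close to 100%. With 142 patients planned in Group B, and all of them connected, 60% would be 0.60 × 142 ≈ 85 patients. Repeated readings over at least 24 hours of treatment would raise these proportions.

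With no dilution at all the formula gives Φ(0) = 50%. Part of the 60% to 100% is therefore reading variation, which a rule without a minimum fall also counts.

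**The case against.** The strongest objection is that an experienced clinician would read jaundice, hemoglobinuria and renal impairment as signs that go with the fall, since they are recognised consequences of hemolysis. On that reading dilution alone yields no cases. Sites must perform at least 10 ECCO2R runs a year, and such staff may not log a change of one or two points after connection as hemolysis. This stands as a limit on the size of the problem. It does not remove the defect, because the sentence does not state that reading and two others fit its words.

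A reader might infer that nearly every connected Group B patient becomes a hemolysis case and that the rate approaches 100%. The documents do not support this. It needs the reading in which a fall alone suffices, a retained prime without red cells, and small reading variation. The 200 mL is also given for the artificial lung; the total circuit prime is not stated.

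A reader might also infer that true hemolysis can no longer be detected. That goes too far. Serious hemolysis follows the serious adverse event route, with attribution by the DSMB, and the free hemoglobin limb can be reported separately. The list is labelled as ECCO2R-related, which already limits an item-level comparison with Group A. No passage says that items are summed, so double counting with the renal item is possible but not established.

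Finally, the full protocol and eCRF may set the reference sample and timing of measurement. Their absence from a journal article is not held against the plan here. The definition itself is stated, and its stated form lets dilution count.

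**Conclusion.** The point holds as a defect of definition. The hematocrit limb has no minimum fall, does not exclude dilution, and carries a list with three possible readings. Where a fall alone suffices, dilution could make a majority of connected Group B patients meet the item: about 60% to nearly 100% on a single pair of readings, and 71 to 99% in the 70 kg case. These figures rest on assumed blood volumes, starting hematocrits, reading variation and handling of the prime. Where accompanying signs are required, the figure for dilution alone is zero. That spread between readings is itself the problem: the non-serious hemolysis rate would be non-specific and would not mean the same thing at each site.

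The effect is confined to this adverse event item and to any overall adverse event rate that includes it. The primary outcome, the sample size, the efficacy analyses and the serious adverse event route are untouched.

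**What to change.** In the Safety section and the eCRF, count hemolysis as an ECCO2R adverse event only when serum free hemoglobin is at least 100 mg/L, the marker the protocol already names. Let an unexplained hematocrit fall, jaundice or hemoglobinuria serve as prompts to measure it. Remove impaired renal function from the hemolysis item, since renal complications have their own.

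Adding only a minimum hematocrit fall would help less. For illustration, with a mean dilution fall of 1.6 points and the same s of 0.5 to 2, a single pair would still reach a 3-point limit in 2 to 31% of patients, and a 5-point limit in 0 to 12%. Confirmation by free hemoglobin avoids this.

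The cost is one change of definition, a free hemoglobin assay when hemolysis is suspected, and slightly lower sensitivity for mild or untested hemolysis. The Trial status section says recruitment had not begun at the time of writing; if the change is made before it begins, there are no data to recode.
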